## 4 STUDY DESIGN

*Leave blank. Text should be included under the relevant subheadings below.*

### 4.1 OVERALL DESIGN

To evaluate the implementation and effectiveness of a multicomponent AI clinical intervention using a patient-level randomized controlled trial (RCT) for underserved patients with DM receiving medical care in FQHC clinics in South and Central San Diego.

- Compared to controls, at both follow-up points, participants receiving DRES-POCAI will report: **Hypothesis 2.1** greater screening rates of DR; expect a 10% improvement in DR adherence rates; **Hypothesis 2.2** will be more likely to (a) complete referrals to the eye specialist, (b) establish early stages of DR, and (c) less likely to present DR complications due to early treatment; and **Hypothesis 2.3** greater (a) knowledge, (b) attitudes, (c) self-efficacy and (d) patient satisfaction about DR, autonomous DR screening, and other DM-related services and resources.
- *Phase of the trial, if applicable*
  - Not applicable
- *A description of the type/design of trial to be conducted (e.g., randomized, placebo-controlled, double-blinded, parallel design, open-label, dose escalation, dose-ranging, adaptive, cluster randomized, group sequential, multi-regional, superiority or non-inferiority design)*
  - This is a randomized controlled trial (RCT). Patients will be randomized into either the intervention or usual care arm when they arrive for their appointment. A simple block randomization design will ensure equal allocations between intervention and usual care arms by clinic and assign participants to equal (1:1) allocation between arms.

Randomization will be performed using a statistical program (random number generator) to allocate study assignments.

- *A description of methods to be used to minimize bias*
  - Drs. [name] and [name] will work closely to manage any potential missing data issues, to measure and correct potential biases, including administrative and fiscal oversight.
- *Dose escalation or dose-ranging details should be contained in **Section 6.1.2, Dosing and Administration***
  - Not applicable
- *The number of study groups/arms and study intervention duration*
  - There will be two study arms as participants will be randomized to the intervention (autonomous DR screening or Standard-of-Care). The intervention is for a period of 1 year.
- *Indicate if single site or multi-site*
  - Single site working with SYHealth. Locations are the King-Chavez and Chula Vista clinics.
- *Name of study intervention(s)*
  - Diabetic Retinal Screening Point of Care Artificial Intelligence by using a special camera and a computer system called EyeArt®.
- *Note if interim analysis is planned and refer to details in **Section 9.4.6, Planned Interim Analysis***
  - Not applicable
- *Note if the study includes any stratifications and if so, identify the stratification planned (e.g. sex, race/ethnicity, age, dose) and refer to details in **Section 9.4.7, Sub-Group Analyses***
  - Not applicable
- *Name of sub-studies, if any, included in this protocol*
  - Not applicable

## 4.2 SCIENTIFIC RATIONALE FOR STUDY DESIGN

The DRES-POCAI study is using a randomized controlled, open-label, parallel superiority trial. The benefit of this trial is that each participant will be randomized to two intervention options, allowing researchers to compare the relative effectiveness of multiple intervention options. The DRES-POCAI study employs a randomized controlled, open-label, parallel superiority trial design. This design is well-suited to achieve the study's aims for several reasons:

**Randomization:** Random assignment of participants to intervention and control groups minimizes confounding variables. This ensures that any observed differences in outcomes are likely due to the intervention itself and not pre-existing differences between the groups. Participants of the DRES-POCAI study will be randomized into two groups: usual care (receive a retinal screening by an optometrist) or intervention group (receive a retinal screening using a special camera and EyeArt® system, *an autonomous AI-based DR screening*). The randomization will occur after consenting and completing the surveys, prior to conducting the DR screening process (for those randomized to the intervention group).

**Open-label Design:** The open-label nature is appropriate given the practical realities of implementing a multi-component intervention with integrated technology. Blinding participants and providers to the autonomous DR screening is logistically difficult. The intervention's immediate results and potential impact on the workflow necessitate an open-label approach.

**Parallel Design:** The parallel design allows for a clear, side-by-side comparison of outcomes between the intervention and usual care groups over time. This establishes the efficacy of the multicomponent approach. Also, this approach streamlines research analysis and clearly compares outcomes within the defined study period.

**Superiority Evaluation:** The primary objective is to determine if the multi-component DRES-POCAI intervention is superior to usual care in increasing DR screenings, early detection, referrals, and patient knowledge/self-efficacy. A superiority trial directly establishes whether the intervention offers significant benefits over the current model.

Overall, the DRES-POCAI study employs a rigorous and well-justified design that balances scientific rigor with ethical considerations and the practical realities of implementation in FQHC settings. The selected study design provides a rigorous and pragmatic framework for evaluating the DRES-POCAI intervention and supports the potential to generate meaningful evidence for improving diabetic retinopathy care in underserved populations.

#### 4.3 JUSTIFICATION FOR DOSE

**Not applicable**

#### 4.4 END OF STUDY DEFINITION

The end of the study is defined as the completion of the last study-related activity at the close of the 2-year study. Participants of the DRES-POCAI study are considered to have completed the study if they have completed all the phases of the study, including the last scheduled DR screening shown in the **Schedule of Activities (SoA), Section 1.3**. A DRES-POCAI participant's individual study period will be considered complete upon the occurrence of the following, whichever comes latest:

**Completion of Baseline Visit:** During the first study visit, participants will complete consent, fill out a brief survey about diabetes care and eye health. At this time, the participant will also be randomized and assigned to the usual care or intervention group.

**Completion of Diabetic Retinopathy Screening:** The intervention group will complete the DR screening using a special camera and the AI system (EyeArt®), the same day of the study visit. The usual care group will complete the DR screening with an eye care provider on a different day and at a different location. The study staff will facilitate this process for participants in the usual care group by assisting them in scheduling appointments for their routine retinal screening. The study staff will provide an overview of the health education sessions, provide engagement and educational materials and schedule the follow-up health education visits with all participants. This step will ensure the completion of this important component.

**Participant Satisfaction Survey (Intervention Group Only):** Participants will complete the end-of-study satisfaction survey.

**Medical visit:** Both study groups will complete a medical visit after the screening. If the medical visit is in-person, then participants will complete it the same day as the screening. If the medical visit is via telehealth, then participants will complete it on a different day after the screening.

**Completion of Health Education Program:** Attendance at all scheduled health education sessions (3 sessions within the 6 months after the study visit) along with completion of any associated post-program evaluation surveys.

**One-Year Follow-Up Screening (Intervention Group Only):** Participants who had a negative initial DR screening will complete a follow-up screening one year after their initial enrollment and the participant satisfaction survey.

**The overall DRES-POCAI study will be considered complete** when participants' recruitment, all follow-up activities (including screenings and surveys) have been finalized, and the collected data has been cleaned, verified, and is ready for analysis. Participants assigned to the usual care group are anticipated to complete their participation within a six-month timeframe, and participants assigned to the intervention group are anticipated to complete the study's research activities at the 12 months from the initial study visit.

Participants may end their participation at any point of the intervention without completing the research activities in the following circumstances:

**Withdrawal:** Refers to participants who voluntarily decide to discontinue their involvement in the study before its completion.

**Lost to Follow-up:** Refers when participants fail to attend scheduled follow-up screenings, and /or are unreachable despite a defined number of contact attempts as defined in the protocols.

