### STUDY DESIGN

**Design:** DRES-POCAI is a patient-level, multi-clinic, randomized controlled, open-label, parallel superiority trial.

**Study Aims and hypothesis:** **Aim 1** of the study is to refine and operationalize a multi-component AI diabetic retinopathy screening intervention (DRES-POCAI) and implementation plan with physicians, clinical staff, and patients from Federally Qualified Health Clinics in South and Central San Diego. **Aim 2** to evaluate the impact of DRES-POCAI implementation in a primary care setting among underserved patients with diabetes mellitus on diabetic retinopathy screening completion. We hypothesize (Hypothesis 2.1) that randomization to DRES-POCAI intervention will result in an increase in diabetic retinopathy screening completion and diabetic retinopathy detection when compared to usual care; (Hypothesis 2.2) that participants receiving DRES-POCAI intervention will be more likely to (a) complete referrals to the eye specialist, (b) establish early stages of diabetic retinopathy, and (c) be less likely to present diabetic retinopathy complications due to early treatment; and (Hypothesis 2.3) that participants receiving DRES-POCAI intervention will demonstrate greater (a) knowledge, (b) attitudes, (c) self-efficacy and (d) patient satisfaction regarding diabetic retinopathy, autonomous diabetic retinopathy screening, and other diabetes mellitus-related services and resources.

**Setting:** Selected clinics from the Federally Qualified Health Center of San Ysidro Health in San Diego County, California.

**Randomization:** Participants will be randomized using a simple block randomization design to ensure equal (1:1) allocation between intervention and standard of care arms by clinic site. Randomization will be performed using a statistical program or randomizer app (<https://apps.apple.com/us/app/choice-maker-random-picker/id1387970091>).

**Blinding:** Study staff and study data analysts will be unblinded due to the intervention activities.

**Study population:** Study participants will be active SYH patients receiving medical care in one of DRES-POCAI's research clinic sites and meet the following inclusion/exclusion criteria.

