| Evaluate the implementation and effectiveness of a multicomponent AI clinical intervention on diabetes and DR knowledge, attitudes, self-efficacy, and patient satisfaction.                                  | 
 
1. A 15 min-survey will be conducted at the baseline and 6 months. The survey will assess patients' knowledge, attitudes about DR (e.g., “Do you think your DM can make you blind”), self-efficacy and (“I am confident that I can: take care of my eyes”). Participants will be asked about their comfort and trust in the use and results of the novel POC-AI screening that does not involve
 
                                                                                                                                            | 
We hypothesize that our intervention strategies will exert their impact on implementation and clinical outcomes through diabetes and DR knowledge, attitudes, self-efficacy, and patient satisfaction (H2.3).
                                                                                                                                                                                                                                                                                                                                                                                                                                                                                                  |

| OBJECTIVES           | ENDPOINTS                                                                                                                                                                                                                                                                                                                                                                                                                                                                                                               | JUSTIFICATION FOR ENDPOINTS                                                                                                                                                                                                                                                                                                                                                        |

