2. **Randomization.** Participants of the DRES-POCAI study will be randomized into two groups: usual care (receive a retinal screening by an optometrist) or intervention group (receive a retinal screening using a special camera and EyeArt® system, an autonomous AI-based DR screening). The randomization will occur after consenting and completing the surveys, prior to conducting the DR screening process. The study coordinator will guide participants through the randomization process using a "Randomizer" app on a tablet or touchscreen device. The participant will press a designated button on the app to initiate random assignment to either the Intervention or Control group. The assigned group will display clearly on the screen for the participant to see.

***Intervention components and procedures.*** The sequence of the study activities that should occur during the intervention includes the health education sessions, administration of surveys and DR screening (***SOPs Surveys, Diabetic Retinopathy Screening and Participant Education***).

1. **Administration of surveys.** Baseline and follow-up surveys will encompass the baseline and 6-month follow up surveys, including the following domains, a) diabetes knowledge and beliefs, b) diabetes self-efficacy and c) diabetes self-management. In addition, participants of the intervention group will be asked to also complete participant satisfaction and experience survey at the check-out visit and at the 12-months follow up when participants return for their annual DR screening using POC-AI. Surveys will be available in English and Spanish (**Appendix 6**).

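### H2.3(d) predicts greater patient satisfaction than in controls, but as planned no comparable control measure is collected and no between-arm analysis is specified

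*Combined protocol and SAP*

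**What the plan says.** **The hypothesis.** Section 4.1 introduces all its hypotheses with "Compared to controls, at both follow-up points, participants receiving DRES-POCAI will report" and then, under H2.3, lists "greater (a) knowledge, (b) attitudes, (c) self-efficacy and (d) patient satisfaction about DR, autonomous DR screening, and other DM-related services and resources". The SAP's study aims repeat it: "participants receiving DRES-POCAI intervention will demonstrate greater (a) knowledge, (b) attitudes, (c) self-efficacy and (d) patient satisfaction regarding diabetic retinopathy".

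**The objective.** The secondary objective in Section 3 is to "Evaluate the implementation and effectiveness of a multicomponent AI clinical intervention on diabetes and DR knowledge, attitudes, self-efficacy, and patient satisfaction". Its justification column cites H2.3. The synopsis carries nearly the same objective.

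**Who is asked.** Section 4.4 lists "Participant Satisfaction Survey (Intervention Group Only". Section 8.1, under administration of surveys, says "participants of the intervention group will be asked to also complete participant satisfaction and experience survey", at check-out and again at 12 months. Section 6.1.1 describes a baseline satisfaction survey, in the intervention-group step, about having been screened with EyeArt.

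**What both arms complete.** Section 8.1 gives the domains of the baseline and 6-month surveys as diabetes knowledge and beliefs, self-efficacy and self-management.

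**How it is analysed.** Section 9.4.3 places satisfaction among the exploratory endpoints and plans to relate it to demographic and clinical characteristics. The SAP's outcome lists contain no satisfaction outcome, and its difference-in-differences analysis is for education and knowledge outcomes.

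**The concern.** A hypothesis about a difference between arms needs the same quantity measured in both arms at the same time, and a stated contrast. For H2.3(d) the plan gives a directional prediction against controls, while its most explicit text on data collection confines the satisfaction survey to one arm. That leaves a hypothesis written into both documents with no route to a test. The trial is open-label, and satisfaction is self-reported by people who know what they received. A favourable score from the intervention arm alone therefore could not separate an effect of the intervention from the level of satisfaction these patients would report anyway.

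**Working it through.** The plan gives no figure for satisfaction, so the check sets the sections side by side.

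1. **Comparator.** Section 4.1 compares with controls at both follow-up points. It does not define those points. The schedule of activities shows post-baseline assessments at 6 and 12 months, so I read them as those two.
2. **Dedicated survey, by arm.** Sections 4.4 and 8.1: intervention arm only. Section 6.1.1: about EyeArt use, which controls do not experience.
3. **Dedicated survey, by time.** Check-out of the study visit and 12 months. The shared follow-up survey is at 6 months. Section 4.4 expects controls to finish within about six months, so no control data are planned for 12 months. The dedicated survey and the shared follow-up survey have no post-baseline time point in common.
4. **Selection at 12 months.** Section 4.4 ties the one-year screening and its satisfaction survey to intervention participants whose first screen was negative. The late score is therefore from one arm and also selected on the screening result.
5. **Shared survey.** The domains listed in Section 8.1 do not include satisfaction.
6. **The Section 3 endpoint.** The 15-minute baseline and 6-month survey is said to ask how satisfied participants are overall with the intervention, with no arm restriction. The item sits beside questions on comfort with and trust in AI screening. Section 4.2 has surveys completed before randomisation, so at baseline there is no intervention to rate in either arm. At 6 months a control would be rating something not received.
7. **Analysis.** Section 9.4.3 and the SAP state no contrast of satisfaction by arm.

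**What a common item could detect.** These are assumptions: a continuous score, two-sided 5% test, 80% power and n respondents per arm. The detectable difference in SD units is (1.96 + 0.84) × √(2/n).

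- n = 361 (the plan's analysis target per arm): 2.80 × √(2/361) = 0.21
- 80% of 361 respond, n ≈ 289: 2.80 × √(2/289) = 0.23
- 60% of 361 respond, n ≈ 217: 2.80 × √(2/217) = 0.27

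The plan gives no response rate for the 6-month survey, and 361 was sized for screening completion. Section 9.4.3 also allows binary or categorical scales. For a binary item near 50%, 2.80 × √(2 × 0.5 × 0.5/361) ≈ 0.10, or about 10 percentage points.

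**Why the choice of item matters.** An item on the eye-screening experience can be answered only by people who were screened. At the plan's 59% and 69% this is 0.59 × 361 ≈ 213 and 0.69 × 361 ≈ 249, giving 2.80 × √(1/213 + 1/249) ≈ 0.26 SD. More importantly, that comparison conditions on the primary outcome and is no longer a comparison of the groups as randomised.

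**The case against.** The other side has a fair case.

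- **The objective names no comparator.** A reader might infer that the secondary objective itself claims greater satisfaction than controls. It does not. It speaks of evaluating effectiveness, and the comparative wording is in H2.3, to which the objective is linked only by its justification column.
- **Control data are not categorically excluded.** A reader might infer that there will be no control observations at all and that a comparison is impossible. The documents do not go that far. Section 3 places a satisfaction item in the common survey without restricting it. Section 9.4.3 describes satisfaction with taking part in the study, which controls could answer. The synopsis mentions satisfaction with other diabetes services, also unrestricted. Section 4.4 mentions evaluation surveys after the education sessions, which all participants attend. The instruments are in an appendix that is not part of the documents.
- **Satisfaction is already treated as exploratory.** Section 9.4.3 says so, the superiority statement in Section 4.2 names knowledge and self-efficacy but not satisfaction, and no test or sample-size claim depends on it.

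All of this limits the point without removing it. The unrestricted mentions conflict with Sections 4.4 and 8.1, and none describes a measure that means the same thing in both arms at the same time. Exploratory status explains the absence of a formal test, but the directional prediction against controls still stands in both documents. Satisfaction with AI screening cannot be asked of controls, but H2.3 also covers other diabetes services and resources. Section 6.3 gives both arms education materials and care coordination support, so that part could be compared.

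**Conclusion.** The point holds in a limited form. As planned, H2.3(d) cannot be tested: the dedicated survey is for one arm and concerns EyeArt, the shared survey lists no satisfaction domain, controls finish before the later satisfaction survey, and no between-arm contrast is specified. The sections that mention satisfaction more broadly conflict with this but do not supply a comparable control measure.

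This rests on the survey content as the documents describe it. If the questionnaires do contain a common satisfaction item, what remains is the conflict between sections and the missing contrast. A reader might also infer that the team intends to present a one-arm score as support for H2.3(d). No section plans that, and Section 9.4.3 describes a different use: refining implementation and identifying barriers.

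The primary endpoint is untouched. The point merits correction because a stated hypothesis has no test and the remedy is small. The 0.21 SD is an assumption-based guide, and it grows with survey non-response.

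**What to change.** Reconcile protocol Sections 3, 4.4, 6.1.1, 8.1 and 9.4.3 on who is asked about satisfaction, with what and when. Then take one of two routes.

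1. **Keep (d).** Add two or three items that do not concern AI to the 6-month survey both arms complete. Choose items every participant can answer whether or not screened, for example satisfaction with diabetes and eye-care services, education and care coordination. State in Section 9.4.3 and the SAP an exploratory contrast by randomised arm. If a detectable difference is quoted, give its assumptions.
2. **Drop (d).** Strike it from H2.3 in Section 4.1 and the SAP, align the secondary objective with that, and report satisfaction descriptively for the intervention arm only.

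Under either route, keep AI-specific and screening-experience items descriptive, because only people who were screened can answer them.

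Route 1 costs about a minute of survey time per participant and a short amendment. Route 2 is a wording change, at the price of giving up the comparison.
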